## Objectives and endpoints

The primary goal of the study is to evaluate sleep disorders in breast cancer patients prior to and during (after 15 fractions/3 weeks) a course of radiotherapy in terms of severity of sleep disorders, distress for the patients and intake of sleeping drugs. These data are used to evaluate the potential effect of habituation to the procedure of radiotherapy and generate hypotheses. Habituation to radiotherapy will likely lead to an improvement (decrease) of sleep disorders during the course of radiotherapy when compared to baseline (prior to radiotherapy). Improvement of sleep disorders is defined as decrease of severity of sleep disorders by at least 2 points on a patient self-rating scale (0 = no problems; 10 = maximum problems) or decrease of distress caused by sleep disorders by at least 2 points on a patient self-rating scale (0 = no distress; 10 = maximum distress) or reduction of the dose of sleeping drugs by ≥25%. The criterion regarding the intake of sleeping drugs was chosen according to another situation of radiotherapy, namely irradiation of painful bone metastases [7]. To obtain the data for these three criteria, patients will complete questionnaires including two self-rating scales and information about intake and doses of sleeping drugs. Additional endpoints include sleep disorders after 5 fractions of radiotherapy, sleep disorders at the end of the radiotherapy course. Moreover, potential risk factors for sleep disorders including the impact of the use of smartphones or tablets at bedtime will be evaluated [3, 4, 8].

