### Eligibility criteria

Inclusion criteria include female gender, histologically proven breast cancer, indication for radiotherapy, sleep disorders (at least 2 points on the sleep disorder self-rating scale), Eastern Cooperative Oncology Group (ECOG) performance score of 0–2, age ≥ 18 years, written informed consent, and capacity of the patient to cooperate (including the ability to complete a questionnaire). Exclusion criteria are pregnancy or lactation and limited legal capacity or being under legal supervision.

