**Fig. 1 Fig1:**
[figure not shown]
Timeline of enrolment, interventions and assessments of the RADIO-SLEEP study

Sleep disorders will be assessed prior to radiotherapy (baseline), and during (after 5 and 15 fractions) and at the end of the radiotherapy course. Evaluation is based on questionnaires including self-rating scales regarding severity and distress due to sleep disorders and information regarding the intake of sleeping drugs. Moreover, the use of smartphones and tablets at bedtime and other factors such as age, type of breast surgery, physical/practical and emotional problems including depression and anxiety, systemic anticancer treatment, side effects of radiotherapy, body mass index, co-morbidity and other factors causing distress will be correlated to sleep disorders [3, 4, 8].2.Adverse Events.

Adverse events will be assessed on an ongoing basis according to Common Terminology Criteria for Adverse Events (CTCAE) version 5.0 [9].

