### Statistical methods for investigated endpoints

The efficacy analysis will be performed on the modified Full Analysis Set defined as all patients receiving radiotherapy with a completed questionnaire at baseline and at least one completed questionnaire after start of treatment. Similar to a previous study, the statistical analyses are mainly descriptive and exploratory [10]. Sleep disorders at baseline and during radiotherapy will be rated using two patient self-reporting scales (sleep disorders and distress) and intake of sleeping drugs. To evaluate the rate of patients with decrease of sleep disorders after 15 fractions of radiotherapy (generally at the end of the third week of treatment), the dichotomized composite endpoint (decrease of severity of sleep disorders, decrease of distress caused by sleep disorders, reduction of the dose of sleeping drugs) is considered, even if patients discontinue radiotherapy prematurely (treatment policy estimand). The number of missing data will be reported. The point estimate of the rate of decrease and the associated 95% confidence interval will be presented. To test whether the rate of decrease is significantly > 10%, the one-sided binomial test at a one-sided 2.5% significance level will be applied.

To further assess the impact of other factors on the primary endpoint, stratified analyses will be conducted. Factors of particular interest include sleep disorders at baseline and use of smartphones or tablets at bedtime. Furthermore, a logistic regression model including the sleep disorder rating scale at baseline, use of smartphones or tablets at bedtime and other factors such as age, type of breast surgery, systemic anticancer treatment, body mass index and co-morbidity will be fitted to identify significant predictive factors for decrease of sleep disorders. Adjusted odds ratios and 95% confidence interval (Wald χ2) will be derived.

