In addition, each component of the primary endpoint will be subjected to statistical analyses to evaluate sleep disorders during the study using descriptive statistical methods. These analyses allow detailed assessments of the scales over time considering potential decrease and increase in sleep disorders. For graphical visualization, Spaghetti-plots and Box-Whisker diagrams will be provided. Changes from baseline will be considered and subjected to descriptive analyses. Friedman and Wilcoxon-signed rank tests may be applied to compare study visits. Cumulative distribution plots of changes from baseline at each visit will be presented; they display a continuous change from baseline on x-axis and the cumulative percentage of patients experiencing that change on y-axis. Analyses will be further stratified by sleeping disorders at baseline and use of smartphones at bedtime. For further exploratory analysis, rates of patients experiencing sleep disorders at each time will be estimated together with associated confidence intervals. These analyses will also be stratified by sleeping disorders at baseline and the use of smartphones at bedtime.

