Moreover, the RADIO-SLEEP study investigates potential risk factors for sleep disorders. In a retrospective study of 175 breast cancer patients receiving adjuvant radiotherapy, occurrence of sleep disorders was significantly associated with higher distress scores, need for psychological support, and greater numbers of emotional, physical or practical problems [4]. Younger age was previously reported to be significantly associated with insomnia in the above-mentioned post-hoc analysis of patients receiving chemotherapy for different cancer types [11]. In a study of breast cancer patients treated with aromatase inhibitors, younger age showed a trend toward increased insomnia [13]. In another study of breast cancer patients, a high insomnia severity index was more common in patients receiving adjuvant chemotherapy than in those receiving adjuvant radiotherapy [14].

A particular focus of the RADIO-SLEEP study is on the impact of electronic media on sleep disorders. The patients complete a questionnaire regarding the use of such devices in general and specifically at bedtime. Negative associations of the use of electronic media at bedtime on sleep quality have been reported for adolescents and adults in general but not particularly for cancer patients [15–19]. Therefore, the RADIO-SLEEP study includes the use of smartphones or tablets at bedtime as a potential risk factor for sleep disorders in the investigated cohort of breast cancer patients.

If the RADIO-SLEEP study demonstrates a decrease of sleep disorders during the course of adjuvant radiotherapy for primary breast cancer, this aspect should be included in the pre-radiotherapy consent discussion with the corresponding patients. Moreover, if additional risk factors for sleep disorders are identified, this will likely lead to earlier psychological support for the patients. If the use of smartphones or tablets at bedtime is identified as a significant risk factor, patients should be advised to change this behavior.

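### Because only patients with sleep disorders are enrolled, risk factors for their occurrence at baseline cannot be estimated, so the stated risk-factor aim and the conditional advice on bedtime device use do not follow from the planned analyses

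*Protocol article*

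**What the plan says.** Four parts of the protocol article bear on this point.

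- **Eligibility criteria.** Inclusion requires "sleep disorders (at least 2 points on the sleep disorder self-rating scale", so nobody below that threshold enters.
- **Objectives and endpoints.** Among the additional aims, "potential risk factors for sleep disorders including the impact of the use of smartphones or tablets at bedtime will be evaluated". The Discussion calls electronic media a particular focus of the study.
- **Planned analyses.** In the Assessments section, device use, age, type of surgery and "other factors causing distress will be correlated to sleep disorders". In the statistical methods section, the one regression model "will be fitted to identify significant predictive factors for decrease of sleep disorders". It contains the baseline rating, bedtime device use and "other factors such as age, type of breast surgery, systemic anticancer treatment, body mass index and co-morbidity". The same section plans that "rates of patients experiencing sleep disorders at each time will be estimated together with associated confidence intervals", stratified by smartphone use at bedtime, and states that "the statistical analyses are mainly descriptive and exploratory".
- **Conclusion drawn.** The Discussion says: "If the use of smartphones or tablets at bedtime is identified as a significant risk factor, patients should be advised to change this behavior". The Discussion paragraph of the Abstract carries the same message.

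**The concern.** A risk factor for a condition is normally found by comparing people who have it with people who do not. The article uses the term in that sense. To motivate the aim, its Discussion cites a retrospective study of 175 breast cancer patients that examined the occurrence of sleep disorders, and it expects that knowing the risk factors will bring earlier psychological support. This trial enrols only patients who already have the condition, and its regression models improvement, which is a different outcome. A factor that causes sleep disorders need not predict recovery by fraction 15, and a predictor of recovery need not be a cause.

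Device use is also observed, not assigned. A patient who cannot sleep may reach for a phone, and a comparison between patients cannot tell that direction from the reverse. What is at stake is a prominent secondary aim and a recommendation addressed to patients. Both could be published as supported even though the plan, followed exactly, cannot support them.

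**Working it through.** **1. The plan's own figure.** Inputs from the sample size section: 48 analysed, null rate 10%, alternative 25%, one-sided 2.5%. The smallest r with P(X ≥ r | 48, 0.10) ≤ 0.025 is r = 10, with exact level 0.0187. Power is P(X ≥ 10 | 48, 0.25) = 0.795, and 0.9005 at 28%. Enrolment is 48/0.95 = 50.5, rounded up to 51. The stated 80%, 90% and 51 are reproduced, so the primary design is not in question.

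**2. Occurrence at baseline.** With severity of at least 2 required, the baseline rate is 100% in users and in non-users. The risk difference is 0 and the odds ratio cannot be estimated, whatever the association in the source population. As an illustration with assumed figures, suppose half of all patients use devices at bedtime, and sleep disorders affect 60% of users and 35% of non-users.

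- Source population: overall rate 0.5 × 0.60 + 0.5 × 0.35 = 0.475; risk difference 0.25; odds ratio (0.60/0.40)/(0.35/0.65) = 2.8.
- Enrolled patients: 100% against 100%, difference 0.

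A large association would leave no trace in the enrolled patients' baseline rates.

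**3. What each planned analysis can address.**

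| Planned analysis | What varies among enrolled patients | Question answered |
|---|---|---|
| Correlation of factors with sleep disorders | Baseline severity 2 to 10; distress; drug use; later scores | Severity among the affected |
| Logistic regression | Improvement yes/no | Predictors of improvement |
| Rates at each visit by smartphone use | Nothing at baseline (at the inclusion threshold); later rates vary | Persistence |
| Change from baseline by smartphone use | Change scores | Course among the affected |

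None of these rows concerns having a sleep disorder at baseline against not having one.

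**4. Precision for the questions that can be answered.**

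- Events in the logistic model: 48 × 0.25 = 12. The text names at least seven covariates (baseline rating, device use, age, surgery, systemic treatment, body mass index, co-morbidity). 12/7 = 1.7 events per covariate. At 28% improvement, 13.4/7 = 1.9.
- The prevalence of device use is not given, so splits of 48 are assumed. With overall improvement of 25% and a two-sided 5% level, power = Φ[(d − 1.96·SE₀)/SE₁], where d is the difference, SE₀ uses the pooled 25% and SE₁ the two separate rates. For 24/24 and d = 0.20 (15% against 35%), SE₀ = √(0.25 × 0.75 × 2/24) = 0.125 and SE₁ = √((0.1275 + 0.2275)/24) = 0.1216. This gives Φ(−0.37) = 0.36.
- Mean severity: the standardized difference detectable with 80% power is (1.960 + 0.842)·√(1/n₁ + 1/n₂).

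| Users/non-users (assumed, either way round) | Power, 20-point difference | Power, 30-point difference | Detectable standardized difference |
|---|---|---|---|
| 24/24 | 36% | 68% | 0.81 |
| 32/16 | 33% | 61% | 0.86 |
| 36/12 | 30% | 54% | 0.93 |

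For 24/24, Fisher's exact test gives 27% and 60%. In the unequal splits, the smaller group is given the higher improvement rate.

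**The case against.** The strongest defence is that the aim can be partly met. Severity ranges from 2 to 10 at baseline, later status is free to vary, and the plan examines both by device use. The Discussion also confines the device question to the investigated cohort. The analyses are declared mainly descriptive and exploratory, and the advice sentence is a conditional remark in the Discussion, not a study procedure or decision rule. The inclusion threshold suits the primary endpoint, whose two rating-scale criteria require a fall of at least 2 points.

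Most of this stands and limits the point. Three stronger readings are tempting, and the documents do not support them.

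- **That the trial can identify no factors related to sleep disorders at all.** This is true only of occurrence at baseline. Severity, change, improvement and persistence can be studied, though imprecisely and in a sample truncated at 2.
- **That the trial plans to tell patients to stop using devices.** The text speaks of changing the behaviour, and only if device use proves to be a significant risk factor.
- **That a known number of comparators is turned away.** One could apply the 45% to 48% prevalence in the Background to the 51 enrolled, but the article does not say that those studies defined sleep disorders by this scale and threshold.

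The exploratory label does not answer the remaining point. It stands beside an aim worded as risk factors for sleep disorders and a sentence that turns a significant association directly into advice.

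**Conclusion.** The point holds for the occurrence of sleep disorders at baseline and for what may be concluded about device use. With a baseline rate of 100% in both groups, the risk-factor aim as worded does not match what the data can show. No planned result would justify the advice sentence, because the planned analyses describe affected patients only and leave the direction of the association open.

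The structural conclusion rests on the eligibility rule alone. If sleep disorders were defined at the visits by a cut-off above 2, baseline rates could vary, but that would be a severity contrast among affected patients. The precision figures (about 1.7 events per covariate, 30% to 36% power for a 20-point difference) rest on the planned 25% improvement rate and the assumed splits. They indicate that a significant result would be fragile and a null result uninformative. The primary analysis is unaffected, so this concerns the secondary aim and its interpretation.

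**What to change.** 1. In the Objectives and endpoints section and in the Discussion, restate the aim as factors, including bedtime device use, associated with baseline severity and with improvement or persistence among patients who have sleep disorders. Label this aim explicitly as hypothesis-generating.
2. In the Discussion and in the Discussion paragraph of the Abstract, replace the advice sentence with a statement that an association with bedtime device use would be a hypothesis for further study, since the direction of effect cannot be established here.

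The cost is wording and a narrower claim. Eligibility, the primary endpoint, the test and the sample size stay as they are.

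Collecting questionnaires from screened patients who score below 2 is not recommended as a remedy. The Questionnaires section asks for the scales only when sleep disorders are present, so these patients may never complete them. It would also add a population to a study that already has ethics approval, and it would leave reverse causation unresolved.

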## Data Availability

Not applicable, since data were not yet generated. The study was registered at clinicaltrials.gov (NCT04879264).

## Abbreviations

CTCAE: Common Terminology Criteria for Adverse Events
ECOG: Eastern Cooperative Oncology Group
RADIO-SLEEP: Sleep disorders prior to and during a course of radiotherapy for breast cancer and the potential impact of smartphones
